#### Bayesian Analysis Plan

In parallel with the frequentist analysis, we will conduct a Bayesian analysis for the primary and key secondary outcomes (cfPWV and VO_₂_max change). The Bayesian model will mirror the mixed linear model used in the frequentist framework to ensure direct comparability of results; specifically, we will include a random intercept at the individual level, fixed effects for the 3 treatment groups, and covariate adjustment for baseline outcome, age, sex, BMI, and systolic blood pressure. By aligning the model structure, any differences between approaches will reflect the inferential framework (use of priors and posterior probabilities) rather than the model specification.

Priors will be specified transparently and chosen to balance prior knowledge with appropriate uncertainty. For the primary treatment effect on cfPWV, we will use a normal prior with a mean of −0.4 m/s and an SD of 0.5 m/s, centered on our expectation derived from an unpublished pilot study, while allowing the posterior to span both benefit and no effect. For VO_₂_max, we will use a weakly informative normal prior with a mean of 0 and an SD of 5 mL/kg/min, covering plausible changes of −10 to 10 mL/kg/min changes. Covariate effects will receive normal(0, 10) priors to mirror the unpenalized adjustments in the frequentist model. Variance parameters, including the SDs of the individual random intercepts and the residual error, will be given half-Normal(0, 5) priors to provide mild regularization of variability estimates.

The likelihood assumes normally distributed postintervention outcomes with participant-specific random intercepts and a common residual variance. We will sample from the joint posterior distribution of all parameters and assess convergence using split-chain diagnostics (eg, agreement across chains) alongside effective sample size thresholds to ensure stable estimation. Posterior summaries will be presented as means and 95% credible intervals for each treatment contrast (AI vs control; HIIT vs control; and AI vs HIIT), providing directly interpretable intervals for the magnitude and direction of the effects.

To aid clinical interpretation, we will also report posterior probabilities for prespecified thresholds of meaningful benefit; for example, the probability that the AI versus control effect on cfPWV is less than −0.2 m/s. Finally, we will evaluate robustness to prior assumptions by repeating the primary cfPWV analysis under a skeptical prior (normal mean 0, SD 0.3 m/s) and an enthusiastic prior (normal mean −0.6, SD 0.3 m/s). These sensitivity analyses will clarify how much the conclusions depend on the choice of prior while preserving the underlying model structure.

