#### Power Calculations

The sample size for this study is based on detecting a change in PWV as measured by the gold-standard reference device (Complior). We also leverage data from the pilot trial. Previous literature has shown that 4 to 8 weeks of aerobic exercise can reduce PWV by −0.35 (−0.68,−0.02) m/s and a 9‐ to 16-week intervention by −0.69 (−1.13, −0.25) m/s [6]. This outcome is heavily dependent on changes in VO_₂_max; for example, a less than 10% improvement will only result in a −0.4 (−0.52,−0.28) m/s change in PWV, whereas >20% improvement will result in a −1.72 (−2.39,−1.04) m/s change. On the basis of the pilot trial, we estimate that the conservative effect (−0.4 m/s) is more realistic, and this is selected as the expected effect size. We also know from the pilot trial that the SD of PWV is quite large relative to the expected effect size. By sampling the pilot data, we obtain an SD of 1.4 m/s for the 30‐ to 65-year-old age group. Using these numbers in standard power calculations [16] results in a required sample size of 193 per group, assuming 80% power at alpha level of .05 (2-sided test). On the basis of pilot, we also know that the correlation between pre- and postintervention PWV measurements in the control group is high (*R*=0.86) and that the correlation is mostly explained by age, sex, BMI, and blood pressure. While the results will be analyzed using a mixed linear model (see below), for which there is no formal power calculation protocol, we leverage the sample size calculations developed by Borm et al [17] for analysis of covariance and adjust the sample size with (1−⍴^2^), where ⍴ is the correlation coefficient for pre- and postintervention outcome variables. This yields a sample size of 50 per group, and to account for attrition, a 10% increase is considered sufficient, leading to a final sample size of 55 per group. A sensitivity analysis illustrates that with a lower-than-expected pre-post correlation (ρ=0.75), the required sample size increases to approximately 94 participants per group (including 10% attrition). On the other hand, with a higher-than-expected pre-post correlation (ρ=0.95), the required sample size decreases to approximately 21 participants per group.

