#### Frequentist Analysis Plan

The primary frequentist analysis will be based on the ITT framework, defined as all randomized participants included in the groups to which they were initially assigned, regardless of adherence or withdrawal. The mixed linear model (see below), which inherently accommodates longitudinal data with missing time points under the assumption of missing at random, will be the primary method used to analyze this ITT population. The ITT analysis provides an unbiased estimate of the intervention’s effectiveness under real-world conditions. However, we expect highly motivated participants to engage the most in their assigned interventions and thus receive the most benefit. This will be investigated in mediator analyses. The intervention may work differently for certain people (eg, men vs women), and these will be studied as moderators. Both mediator and moderator analyses are described below.

The difference between the AI group and the Oura Ring only group will be considered the primary comparison, while differences across other group pairs will be exploratory. The primary analysis will be based on a mixed linear model, which is an appropriate method for analyzing repeated measures data while accounting for individual-level variability. This model will be used to assess the effectiveness of the interventions and compare the mean postintervention cfPWV and VO_2_max across the 3 study groups. We will assume that any missing data are missing at rMissing At Random. The results will be presented with full, numeric *P* values, mean differences, and 95% CIs, avoiding an arbitrary (eg, *P*=.05) dichotomy into statistically “significant” and “insignificant.” No formal correction for multiple comparisons will be applied. Instead, we used a linear mixed model, which induces partial pooling of group-level estimates. As discussed by Gelman et al [18], this approach reduces the risk of overestimating spurious differences that can arise from multiple comparisons, thereby mitigating concerns related to multiple testing. Accordingly, we will focus on effect sizes and their uncertainty rather than dichotomous significance testing.

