To evaluate how strongly candidate mediators account for the intervention-outcome association, each mediator will be entered sequentially into the previously specified linear mixed model, and the resulting change in the intervention regression coefficients will be examined. The proportion of attenuation attributable to each mediator will be calculated as follows: (1−[regression coefficient adjusted for the mediator/regression coefficient adjusted for the determinant])×100%. In parallel, we will assess the incremental predictive value contributed by the intervention effects beyond their presumed mediators. The mediation analyses will be conducted in the full participant population across all randomization groups.

In addition to mediator analyses, we will evaluate prespecified moderators (eg, sex, age, baseline cfPWV, and cardiorespiratory fitness) by extending the primary linear mixed model to include the group×time×moderator interaction. For binary moderators (eg, sex), inference will focus on the group×time×sex term; for continuous moderators, variables will be mean-centered and effects probed at interpretable values (eg, mean, 1 SD) via model-based marginal means and simple-slope contrasts. When an interaction shows evidence of effect modification, we will present stratified (subgroup) estimates and contrasts within moderator levels for interpretation.

These secondary analyses are crucial for exploring potential effects that may be obscured by the ITT analysis, particularly if adherence is low. They will be clearly identified as exploratory and will complement the primary ITT analysis.

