## Results

Recruitment for the study began in October 2024 and will conclude once 165 men and women have been recruited. Data collection for the study is scheduled to conclude in March 2026. Three participants have withdrawn from the study during the intervention phase. Data management is ongoing.

The peer-reviewed study protocol will be accessible via the journal’s website and the study’s site at ClinicalTrials.gov. A separate statistical analysis plan is not currently planned as all necessary details are included within this protocol.

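### The primary mixed model is specified inconsistently: one part describes ANCOVA with a redundant random intercept, another a two-visit model, and combining them gives wrong standard errors

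*Protocol article*

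**What the plan says.** Both co-primary outcomes are measured at baseline and once more at 12 weeks (Abstract, Methods; Study Measurements). The repeated cfPWV readings at a visit are averaged before analysis (Pulse Wave Velocity and Pulse Wave Analysis). Each person therefore has one post-intervention value per outcome.

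Four places then bear on the primary model:

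- **Bayesian Analysis Plan.** "The likelihood assumes normally distributed postintervention outcomes with participant-specific random intercepts and a common residual variance". The listed terms are a random intercept per person, group effects and "covariate adjustment for baseline outcome, age, sex, BMI, and systolic blood pressure". No time term is listed. The section says that this structure matches the frequentist model.
- **Frequentist Analysis Plan, primary analysis.** All randomized participants are to be included. The mixed model "inherently accommodates longitudinal data with missing time points under the assumption of missing at random". It compares post-intervention means across the groups.
- **Frequentist Analysis Plan, moderators.** These are tested by "extending the primary linear mixed model to include the group×time×moderator interaction".
- **Power Calculations.** The trial is sized with the ANCOVA factor (1−ρ²).

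The Results section adds: "A separate statistical analysis plan is not currently planned as all necessary details are included within this protocol".

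**The concern.** No single model meets all four descriptions. A likelihood for the post-intervention value with baseline as a covariate has one row per person, so it has no time dimension, no repeated measures and no way to use a person whose 12-week value is missing. A group×time×moderator term needs the baseline value as an outcome row. If baseline becomes an outcome and also stays as a covariate, it is used twice and the assumption of a common residual variance fails.

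This matters because the text governs both co-primary outcomes and both inferential frameworks. The protocol promises that differences between the frameworks will reflect inference and not specification, and that needs one fixed model. An analyst could defend several models from this text. Some are correct, and at least one that combines the stated elements is clearly anticonservative.

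**Working it through.** **Inputs (Power Calculations).** Effect: "we estimate that the conservative effect (−0.4 m/s) is more realistic". SD: "we obtain an SD of 1.4 m/s for the 30‐ to 65-year-old age group". Pre-post correlation ρ = 0.86; two-sided alpha 0.05; 80% power; 10% attrition.

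**The plan's own figure.** n = 2(1.96 + 0.8416)² × 1.4² / 0.4² = 192.3, so 193. Then 193 × (1 − 0.86²) = 193 × 0.2604 = 50.3, stated as 50, and 50.3 × 1.1 = 55.3, stated as 55. The sample size reproduces.

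**Reading A: the Bayesian section taken literally, one row per person.** Only the sum of intercept and residual variance enters the likelihood.
- On a simulated dataset the log-likelihood was −153.075 whether the intercept took 0, 25, 50, 75 or 100% of the variance. The effect (−0.442) and its SE (0.143 at the fixed total variance) were the same at every split.
- With the stated half-Normal(0, 5) priors, the effect posterior was −0.340 (SD 0.131) with or without the random intercept.
- A REML fit returned an arbitrary 50/50 split and a Hessian that was not positive definite. The baseline-slope SE was 0.011 against 0.045 by least squares. The treatment SE was close in that dataset (0.134 against 0.136), but output with such a warning cannot be relied on.
- At 10% attrition, 165 × 0.9 = 148.5, so about 148 of 165 contribute.

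**Reading B: both visits as outcomes, baseline also a covariate, group main effects only.** The group coefficient averages a zero difference at baseline with the week-12 effect: (0 − 0.40)/2 = −0.20. With 55 baseline and 49.5 week-12 values per arm it is −0.40 × 49.5/104.5 = −0.19.

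**Reading C: as B, plus group×time.** The fitted common slope on baseline is near (1 + 0.86)/2 = 0.93. In units of σ²:
- residual variance at baseline: 0.07² = 0.0049
- residual variance at week 12: 0.2604 + 0.07² = 0.2653
- pooled: (0.0049 + 0.2653)/2 = 0.1351
- covariance between visits: 0.07 × (−0.07) = −0.0049, so the random-intercept variance is driven to zero (about 99% of fits)

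The model thus gives the week-12 contrast an SE of about √(0.1351/0.2653) = 0.71 of its true value.

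**Reading D: both visits, group×time, no baseline covariate.** The variance factor is 2(1 − 0.86) = 0.28, so 193 × 0.28 = 54.0 evaluable per arm. At 50 per arm the SE is 1.4 × √0.28 × √(2/50) = 0.148, z = 0.40/0.148 = 2.70, and power is about 77%. ANCOVA gives 79.9%.

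**Simulation.** 4,000 trials per scenario, 50 completers per arm, REML. The HIIT effect was assumed to be 0.8 of the AI effect; age, sex, BMI and blood pressure were left out.

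| Model and coefficient | Mean estimate (true −0.40) | Mean SE / empirical SD | Type I error |
|---|---|---|---|
| ANCOVA, no random intercept | −0.398 | 0.99 | 5.5% |
| B, group main effect | −0.199 (coverage 22.6%) | 1.02 | 4.8% |
| C, week-12 group contrast | −0.398 | 0.70 | 17.4% |
| C, group×time | −0.398 | 0.97 | 5.4% |
| D, group×time | −0.398 | 0.985 | 5.1% |

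With 55 per arm and 10% missing at week 12, the week-12 contrast in C had a mean SE of 0.101 against a true 0.143 to 0.146, and a type I error of about 17%. The group×time coefficient in C had a type I error of 6.3 to 7.1% across runs. A two-visit model with a common baseline mean had SE 0.143 against 0.144, a type I error of 5.3% and the same power as ANCOVA.

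**The case against.** A reader might infer that the primary analysis is not identified, or that every reading of it fails. The documents do not support that.

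- **Identification.** Under the literal model only the split of a nuisance variance is unidentified. The treatment effect equals ANCOVA, which is the analysis that the sample size assumes, and the proper priors keep the Bayesian posterior proper. A failed REML fit would usually announce itself. This stands.
- **A valid reading exists.** D fits the repeated-measures wording of the frequentist section and costs about 3 points of power. This stands, although D contradicts the baseline adjustment in the Bayesian section.
- **The halved effect.** Reading B conflicts with the statement that the outcomes are post-intervention and with the moderator text, which presupposes group×time. It follows only if the listed terms are applied to two-visit data, so it is a hazard of the wording and not the plan's evident intent.
- **All randomized participants.** The claim fails only under the one-row model. Complete-case ANCOVA is still valid if data are missing at random given the covariates, and baseline-only participants add almost no information. The 10% is a planning allowance; the Results section reports three withdrawals so far. This stands, but the missing-data statement is still wrong for the model as written.
- **No threshold.** The protocol disclaims significance cut-offs and calls its conclusions exploratory. That does not rescue an SE about 30% too small, because the confidence intervals it relies on are then too narrow.

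The inconsistency itself remains, and the protocol rules out the usual reply that an analysis plan will settle it.

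**Conclusion.** The primary model is stated inconsistently, and this is an error as written rather than detail left for later. The size depends on the reading:

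- **One row per person:** a correct treatment effect if the fit succeeds, with a redundant random intercept and a missing-data claim that does not hold.
- **Two visits without the baseline covariate:** valid, with about 54 rather than 50 evaluable per arm needed.
- **Two visits with the baseline covariate kept:** type I error of about 17% for the week-12 contrast and 6–7% for group×time. Group main effects alone would roughly halve the estimate.

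These figures rest on the plan's SD, correlation and effect for cfPWV, on normal data, on 10% missing where stated, and on leaving out the further covariates. They do not show that the trial is undersized: 193, 50 and 55 reproduce.

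**What to change.** State one model for both frameworks and name the coefficient that is the treatment effect, so that the treatment prior attaches to the same quantity. Either choice below serves:

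1. **ANCOVA.** Regress the week-12 value on group, baseline outcome and the other covariates at baseline. Delete the random intercept, correct the missing-data claim, state how missing week-12 values are handled, and replace group×time×moderator with group×moderator.
2. **Two-visit model.** Use baseline and week-12 values as outcomes, with a common baseline mean across arms, an unstructured 2×2 within-person covariance, and group×time at week 12 as the effect. Remove baseline outcome as a covariate. The moderator term and the inclusion of people with baseline data only can then stand.

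Both keep the ANCOVA precision on which the sample size rests. The cost is a paragraph of analysis text, best settled before group codes are released. No new data are needed and no power is lost.

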#### Process Evaluation

##### Overview

The study will include a process evaluation to examine (1) the implementation of the intervention study, (2) the context that may have influenced the study and its findings, and (3) the mechanisms of the intervention’s effects.

Process evaluations are well established in public health and health service research, where they are considered essential to understanding how complex interventions achieve their effects [19,20]. “Complex interventions” are health interventions that have many potential “active ingredients.” A complex intervention combines different components in a whole that is more than the sum of its parts. While process evaluation is commonplace in public health and service settings, its purpose and aims are equally relevant for evaluating any intervention in which multiple factors and influences may shape trial outcomes. In this study, the interventions are complex in that they integrate structured exercise, technology-supported self-monitoring, AI-delivered behavioral support, and participants’ own contextual circumstances.

Implementation: Implementation will be assessed to understand how delivery of the interventions was achieved, what was delivered, and to whom. Trial records will be used to monitor the numbers randomized, adherence to baseline and follow-up assessments, and attrition across groups. Intervention delivery will be captured through adherence to HIIT sessions and the number and frequency of Advisor interactions in the AI coach group.Context: Context will be explored to identify external and personal factors that influenced participant engagement with the interventions. Poststudy interviews with a subsample of approximately 8 participants from each study arm will investigate participants’ life circumstances (eg, health, family or work demands, and seasonality) that may have shaped their ability to participate. In addition, the technological environment will be considered: as the study is conducted with a commercial wearable and companion app, feature updates or design changes released during the trial may alter how participants interact with the intervention. Such changes will be documented and examined as contextual influences, while participants’ perceptions of these changes will be captured through the interviews.Mechanisms of impact: Mechanisms of impact will be examined to understand how participants engaged with and experienced the interventions and how these contributed to perceived or actual changes in behavior. Poststudy interviews will explore participants’ perceptions of changes in exercise habits, motivation, and use of the Oura Ring and the AI coach. Questionnaire data from the RM4-FM (body composition measurement experiences) and the ESES will provide descriptive markers of participants’ experiences and self-efficacy across groups. In addition, Advisor chat logs will be summarized descriptively to identify common conversation topics, user trajectories, and pain points.

##### Qualitative Process Evaluation

Interview transcripts will be analyzed using reflexive thematic analysis, supported by AI tools, such as LLM for coding assistance, clustering, and retrieval of exemplar quotes [21-23]. Final theme development and interpretation will remain human led. Coding will proceed iteratively, with codes and themes discussed within the research team to ensure reflexivity and consistency. A subset of transcripts will be double coded to enhance credibility. Interactive visual tools used during interviews will also generate participant-drawn trajectories of experience and well-being, which will be incorporated into the analysis.

##### Quantitative Descriptive Process Evaluation

Questionnaire data will be summarized descriptively to provide additional context for interpreting study outcomes. RM4-FM and ESES scores will be reported as means and SDs (or medians and IQRs if nonnormally distributed) at baseline and 12 weeks for each group. Within-group descriptive changes over time will be summarized. Engagement metrics, including Oura App analytics and frequency and length of Advisor chat interactions, will be reported descriptively. Advisor chat analytics will be generated using Nebuly, a user analytics platform for LLM applications that automatically captures conversational interactions while anonymizing personal information; these data will provide aggregate summaries, such as the number and length of conversations, common user intents, and interaction drop-off points. These data are not intended for mediation or moderation analyses but to contextualize participants’ reported experiences of the study and interventions.

### Ethical Considerations

The Oura Ring is strictly for consumer use only and not intended to be a medical device. The study plan has been approved by the Regional Medical Research Ethics Committee of the Eastern Finland Collaborative Area (approval 207/13.00/2024). The study aims, design, progression, and the content of study visits will be discussed with the study participants in detail. They will also receive written information on these aspects. The participants will give their written consent to participate in the study. They have every right to withdraw from the study at any point without providing a reason.

There will be no significant risks to participate in this study. An experienced exercise physiologist will supervise each ergospirometry test, and each HIIT session will be supervised by students in health sciences or somebody from the KuLTu personnel adequately trained for the task. Personnel have up-to-date first aid skills, and a defibrillator will be available during the ergospirometry tests and also during supervised HIIT sessions. The well-being of the participants will be followed during the study visits.

Participants are invited to participate in the process evaluation interviews voluntarily, but they can withdraw their consent at any stage. The qualitative interview methods used in this study are typical of qualitative research and are widely used. The researchers conducting the study have several years of experience in conducting similar studies and are thoroughly familiar with the methods used.

Interviews that address health and personal life topics always carry the possibility that questions may touch on sensitive and potentially emotional topics for the interviewees. Interviewees are not obliged to answer any questions they do not wish to answer and will be reminded of this verbally during the interview.

Owing to the low-risk nature of the exercise intervention and the nonmedical classification of the device features, no formal, independent Data Monitoring Committee is considered necessary. Any participant who experiences harm from trial participation will be provided with necessary ancillary care and follow-up by the Kuopio University Hospital. There is no provision for financial compensation other than that mandated by local research ethics guidelines.

Any significant protocol amendments (eg, changes to eligibility, outcomes, or analysis) will be communicated to the Regional Medical Research Ethics Committee of the Eastern Finland Collaborative Area and the ClinicalTrials.gov registry and will be detailed in the final study report.

